## Abstract

**Background:**

The concept of attachment is relevant for the onset and development of chronic pain. Insecure attachment styles negatively affect therapeutic outcome. Insecurely attached patients seem to be less able to sustain positive effects of a multimodal treatment program. However, it has never been tested before if an attachment-oriented approach can improve treatment results of insecurely attached patients in a multimodal outpatient setting. To test this assumption, we compare the short- and long-term outcomes for pain patients who will receive multidisciplinary, attachment-oriented treatment with the outcomes for patients in a control group, who will receive the multidisciplinary state-of-the-art treatment.

**Methods:**

Two patient groups (baseline, attachment intervention) are assessed before treatment, after treatment, and at a 6 month follow-up. The study is conducted in a block design: After data collection of the first block (controls) and before as well as during data collection for the second block (treatment group), the health care personnel of the outpatient pain clinic receives training on attachment theory and its use in the therapeutic context. Pain intensity as measured with visual analogue scales and physical functioning will serve as the primary outcome measures.

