### Sample size calculation

We calculated the necessary sample size for each of our two subsamples (intervention and control) with the G*Power Analysis software program for two-sample t-tests [17], and by reference to our primary outcome measure (pain intensity). Based on the results of our pretests, we expected a small to medium effect of 0.4 for the comparison of the two groups (with an alpha level = 0.05, two tailed, β = 0.2). Results indicate that at least 93 participants are required for each group, for a total of 186.

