### Statistical analysis

Descriptive statistics will be used to describe the characteristics of the study sample. Analysis of variance will be used for the evaluation of the changes of the continuous outcomes pain intensity and physical functioning (T1-T2, T1- T3). Research condition (attachment style and study group), will be used as independent variable. Demographic variables such as sex, age, education and clinical variables such as opioid intake and comorbidity will be entered as covariates. Partial regression coefficients will be used to determine if the “working alliance” mediates the effect of attachment on the continuous outcomes (pain and physical functioning).

Missing data on the questionnaires will be handled according to the questionnaire protocol.

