### Primary outcome measures

With two Visual Analogue Scales, we assess the pain intensity at present and within the previous week. Patients are also asked to indicate the number of days they experienced pain, and the number of days they experienced strong pain, both within the previous month. Physical functioning will be assessed with the Oswestry Disability Index by Mannion et al. [34], which has been specifically developed for use with pain patients. Also, we included a widely used German short version of the Health Survey to assess physical functioning and health-related quality of life more generally [8].

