#### Pain intensity and functional impairment

Subjective pain intensity over the preceding week was measured on a visual analogue scale (VAS; [26]) ranging from 0 (no pain) to 100 (worst imaginable pain). Each patient indicated a position on the VAS in response to the question “How severe was your pain on average in the last seven days?” The VAS is a valid and reliable instrument for measuring the intensity of pain.

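### The primary outcome is stated as one, two and six measures, with no primary interval, so the article does not fix which result decides the trial

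*Protocol article*

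**What the plan says.** The protocol article defines the primary outcome in several places, and they differ.

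- **Abstract, Methods:** two outcome domains. "Pain intensity as measured with visual analogue scales and physical functioning will serve as the primary outcome measures". No instrument is named for functioning and no time point is given.
- **Sample size calculation:** one outcome, in the singular. The calculation was done "by reference to our primary outcome measure (pain intensity"), "with an alpha level = 0.05, two tailed, β = 0.2".
- **Primary outcome measures:** six measures. "With two Visual Analogue Scales, we assess the pain intensity at present and within the previous week"; the paragraph then adds the number of days with pain, the number of days with strong pain, the Oswestry Disability Index (ODI) and the SF-12.
- **Pain intensity and functional impairment:** one scale only. "Subjective pain intensity over the preceding week was measured on a visual analogue scale", scored 0 to 100 as a seven-day average.
- **Statistical analysis:** analysis of variance on the changes in "pain intensity and physical functioning (T1-T2, T1- T3"). Neither interval is called primary.
- **Background, hypotheses:** the first hypothesis concerns the reduction in pain intensity from before to after treatment, which is T1–T2.

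**The concern.** The primary endpoint is the result by which a trial is judged, and it consists of a measure and a time point. Here the number of measures is one, two or six depending on the section, and the interval is open. A separate analysis plan could add a testing procedure, but it could not make these sections of the article agree.

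What is at stake is the meaning of a positive result. Only one comparison was sized. If several results may each be presented as the primary one, the chance that at least one is significant with no true effect exceeds the 0.05 used for that comparison. The groups are also recruited one after the other without randomisation, so a clear advance choice of endpoint is one of the few safeguards available.

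**Working it through.** **Inputs from the article.** Two-sided alpha 0.05, power 0.80, standardised effect 0.4 and 93 per group (Sample size calculation); six measures (Primary outcome measures); two intervals, T1–T2 and T1–T3 (Statistical analysis). **Assumption.** The article gives no correlations between test statistics, so I use a common correlation r from 0 (independence) to 0.7.

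**Step 1: the plan's own figure.** It says "we expected a small to medium effect of 0.4 for the comparison of the two groups" and that "at least 93 participants are required for each group, for a total of 186". A two-sample t-test with effect 0.4, two-sided alpha 0.05 and power 0.80 needs 99.08, so 100 per group; 93 per group gives power 0.774. An effect of 0.413 would give 93, so rounding of the effect may explain the gap. That is a separate matter. What counts here is that the calculation covers one comparison at 0.05.

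**Step 2: count the tests on each reading.**

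- One: seven-day VAS, T1–T2. This combines the first hypothesis, the sample-size outcome and the scale that is described.
- Four: seven-day VAS and ODI × 2 intervals = 2 × 2.
- Eight: two VAS items, ODI and SF-12 × 2 intervals = 4 × 2.
- Twelve: all six listed measures × 2 intervals = 6 × 2.

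**Step 3: chance of at least one false positive, if each test may succeed at 0.05.** For independent tests this is 1 − 0.95^k. For correlated tests it is the probability that at least one of k equicorrelated standard normal statistics exceeds 1.96 in absolute value.

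| Tests k | Independent | r = 0.5 | r = 0.7 |
|---|---|---|---|
| 1 | 5.0% | 5.0% | 5.0% |
| 4 | 1 − 0.95^4 = 18.5% | 15.6% | 13.0% |
| 8 | 1 − 0.95^8 = 33.7% | 25.0% | 19.1% |
| 12 | 1 − 0.95^12 = 46.0% | 32% | 23% |

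The independence column is an upper end. Two pain scales, and two changes from the same baseline, will be positively correlated. The table counts group comparisons only; tests of attachment style or of its interaction with group are left out.

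**The case against.** Four objections deserve weight.

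1. **No stated error rate is broken.** A reader might infer that the trial promises a 5% overall rate and fails to keep it. The article does not support this. The 0.05 is an input to one sample-size calculation, and no overall rate is claimed. Allocation of alpha is commonly left to an analysis plan, so its absence from an article is not itself a fault. This objection stands in full.
2. **Twelve primary tests are not clearly planned.** The analysis section names only pain intensity and physical functioning. Table 1 labels the day counts as pain frequency and lists the SF-12 under emotional distress as well as functioning. Twelve depends on the heading of the outcome section, so it is an upper count. Without the day counts it is eight.
3. **Not every reading inflates the error.** Taking the sample-size section, the first hypothesis and the described VAS together gives one test at 5%. That is correct. But the article never says that this reading governs, and its abstract and outcome section say otherwise.
4. **Sizing on one of two primary outcomes is ordinary practice.** It is, and the sections do share the two domains of pain and functioning. That explains part of the difference. It does not explain the singular wording, the second VAS item or the unranked intervals.

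A reader might also infer that the endpoint was left open after the results had been seen. The Trial status section dates data collection, not the writing of the analysis plan, and an earlier internal plan may exist. Nothing shows that any comparison had been looked at. Finally, a rule requiring all measures to succeed together would remove the inflation, but none is stated.

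**Conclusion.** The inconsistency is real and should be resolved: the article gives one, two and six primary measures, two VAS items against one described, and two intervals without a ranking. The trial's criterion for success is therefore not determined by the text.

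The statistical consequence is conditional. It assumes that any one eligible result could be claimed as primary at 0.05. On that assumption the false-positive chance runs from 5% on the narrowest reading to 46% on the widest with independent tests. With plausible positive correlation the multi-test readings are lower, but even four tests at r = 0.7 give 13%, more than twice 5%. The finding rests on the contradictory definitions and not on the lack of a multiplicity adjustment.

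**What to change.** Name one primary endpoint, in the same words, in the abstract and in the sections on sample size, statistical analysis, primary outcome measures and pain intensity.

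- **Primary endpoint.** The choice best anchored in the text is the T1–T2 change in the 0–100 VAS for seven-day average pain. The first hypothesis gives the interval, the sample size section gives pain intensity and the measure description gives the scale. The sample size section itself states neither recall period nor interval, so this remains the sponsor's decision to make explicit. The article's emphasis on long-term outcome could be argued for T1–T3.
- **Other measures.** Make present-pain VAS, the two day counts and SF-12 secondary. Test VAS T1–T3 and ODI at both intervals in a stated fixed order, each at 0.05 only if the preceding test succeeds. The order is for the sponsor to choose; the documents do not imply one.
- **Timing.** Fix and date the choice before any between-group comparison. Disclose that pre- and post-treatment assessments were complete in the control group by October 2013 and in the intervention group by December 2015. Naming a T1–T2 endpoint now is therefore a clarification after data collection and should be reported as such.

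**Cost.** No new data are needed and the first test keeps its full alpha and power. The price is that later tests can no longer stand alone as primary results. Keeping all twelve as primary with a Bonferroni correction (0.05/12 = 0.0042) would cost far more: with effect 0.4 and 93 per group, power per test would fall from 77% to 43%.

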**Discussion:**

The design of our study allows for a continuous exchange of experienced team members, which may help bring about concrete attachment related guidelines for the enhancement of therapeutic outcome. This would be the first attempt at an attachment-oriented improvement of multimodal pain programs.

**Conclusion:**

An attachment-based approach may be a promising way to enhance long-term treatment outcomes for insecurely attached pain patients.

**Trial registration:**

DRKS00008715 (registered on the 3^rd^ of June 2015).

## Background

Today, it is widely acknowledged that the onset and development of chronic pain syndromes is a result of complex interactions between biological, psychological and social influences, including patients’ beliefs about their self-efficacy, hypervigilant monitoring of bodily sensations, familial conflict or social support [19, 21, 22, 32]. If patients, for example, exhibit maladaptive behavioral or cognitive responses to acute episodes of pain, the pain may become chronic, thus affecting the long-term course [41].

Attachment theory provides a useful framework to classify patients’ relatively stable cognitive, emotional and behavioral response styles to stressors (such as pain), which have been successfully linked to disease processes in general [24, 35] and to diagnosis and processes of pain-related diseases in particular [37, 43]. Based on their dominant response patterns, adults can be classified to one of four attachment styles - one *secure* style, and the three insecure styles *dismissing*, *preoccupied*, and *fearful* [2, 38]. Bartholomew and Horowitz developed a model based on these four attachment styles (for a simplified overview, see Fig. 1). This model shows that adults with a secure style see themselves and others in a positive way, whereas fearful adults tend to see themselves and others in a negative way [2].

**Fig. 1 Fig1:**
[figure not shown]
Attachment Model

These attachment styles relate to patients’ stress responsiveness, their beliefs about their ability to cope with the experience of pain, or specific interaction patterns with spouses or health care personnel [14, 39]. Patients with insecure attachment patterns report higher levels of pain [36, 51], higher degrees of disability [12], lower levels of pain efficacy [39], show less functional and more dysfunctional coping strategies such as catastrophizing [10], and greater levels of depression and anxiety [1, 40]. Bartholomew and Horowitz [2] also demonstrated that secure and dismissing individuals report higher measures of self-esteem on Rosenberg’s Scale [44] compared to fearful and preoccupied individuals. Previous findings suggest that attachment security can be associated with higher self-esteem, whereas, low self-esteem seems to be more related to insecure attachment patterns [5, 11, 18].

These findings are especially relevant given that insecure attachment styles are overrepresented in patients suffering from chronic pain [12, 46]. Attachment insecurity also negatively influences the working alliance with health-care professionals [4], and outcome in psychosocial interventions [31].

To date, the knowledge about attachment concepts has not been used to improve pain treatment outcomes with the help of a differential approach based on individual attachment styles. Therefore, we will compare the short- and long-term treatment outcomes for pain patients who will receive multidisciplinary, attachment-specific treatment with the outcomes for patients in a control group who will receive the multidisciplinary state-of-the-art treatment (for a simplified overview, see Fig. 2). Our preliminary hypotheses were formulated based on the abovementioned information.

**Fig. 2 Fig2:**
[figure not shown]
Attachment-based Working Alliance Model

Patients in the intervention group, who receive an attachment-based multidisciplinary treatment, will report a larger mean reduction of the pain intensity between pre-treatment and post-treatment assessments than patients in the control group, who receive the state-of-the-art multidisciplinary treatment. It is expected that this larger reduction of the pain intensity in the intervention group compared to controls can be specifically attributed to better outcomes for the intervention group patients than control group patients who have been assessed with insecure attachment styles. Moreover, patients with an insecure attachment style and patients with more attachment anxiety are expected to report higher levels of pain intensity as well as physical functioning.The intervention is specifically designed to improve the therapeutic relationship and to hereby improve treatment outcomes. Therefore, we expect to find improved ratings of the relationship (working alliance) between patients and therapists in the intervention group which will mediate the treatment outcomes pain intensity and physical functioning.There will be a greater decline in help-seeking behavior and use of medication in the intervention group compared to the control group from pre-treatment to after the 6-month follow-up. This will be especially hypothesized for insecurely attached patients in the intervention group.Subjective self-awareness of the patients particularly with regard to self-esteem will be expected to change to a greater extent in the intervention group compared to the control group.

## Methods

### Design

The study is conducted in a block design with two patient groups as blocks (baseline, attachment intervention) and 3 assessments T1, T2, and T3 (before treatment, post-treatment, and at a 6 month follow-up). We decided against a randomized controlled trial because (a) we had ethical concerns with a design that would put patients on a waiting list for several months, and (b) a block design ensures that the intervention’s effects only influence the outcomes of the treatment group: After collection of data for the control group, the health care personnel of the outpatient pain clinic receives training sessions on attachment theory and its use in the therapeutic context. These training sessions will not be carried out until data collection for the control group will be complete. More attachment-related training sessions alternating with supervision meetings will be held on a monthly basis to assist the therapeutic team in the practical application during data collection for the second sample, the treatment group. During our weekly team meetings, the case reviews will be complemented with a discussion on the individual attachment style of each patient. Also these meetings will be used to collect situations, which are perceived to be critical for the forming of a working alliance by the therapeutic team (for example, situations in which the patient misses entire therapeutic sessions or appears too late to them on a regular basis). These critical situations will be subsequently used to structure the discussions of individual cases in the bi-monthly training sessions.

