## Conclusions

### Trial status

Recruitment of patients for the control group started in March 2012. Pre- and post-treatment assessments were complete by Oct. 2013 with a total of 184 patients who received a questionnaire at T1 (for an overview of the recruitment process including dropout numbers, see Fig. 3). The 6-month follow-up questionnaires of the control group were completely sent out by May 2014. Each team member received monthly intervention training sessions between Nov. 2013 and May 2015. For an overview of the received attachment training, see Table 2. Recruitment of patients for the intervention group started in March 2014. Pre- and post-tretments were complte by Dec. 2015 with a total of 194 patients who received T1. The 6-months follow-up questionnaires of the interventions group will be completely sent out by June 2016.

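### Staff training overlapped the control group's 6-month follow-up, so the stated protection from spillover holds for T1-T2 only; calendar period, a separate issue, is not listed as a limitation

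*Protocol article*

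**What the plan says.** The Design section gives the study "3 assessments T1, T2, and T3 (before treatment, post-treatment, and at a 6 month follow-up". It offers as one reason for not randomising that "a block design ensures that the intervention’s effects only influence the outcomes of the treatment group", and supports this with a rule on timing: "These training sessions will not be carried out until data collection for the control group will be complete". The Methods part of the Abstract places training in the same order: "After data collection of the first block (controls) and before as well as during data collection for the second block (treatment group".

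The Trial status section gives the dates. "Recruitment of patients for the control group started in March 2012", and control T1 and T2 were complete by October 2013, with 184 patients having received T1. On training: "Each team member received monthly intervention training sessions between Nov. 2013 and May 2015". On control follow-up: "The 6-month follow-up questionnaires of the control group were completely sent out by May 2014". Intervention recruitment began in March 2014, and its T1 and T2 were complete by December 2015, with 194 patients.

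The Statistical analysis section evaluates change in pain intensity and physical functioning over both T1-T2 and T1-T3. Table 1 shows help-seeking and medication use at T1 and T3 only.

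**The concern.** The timing rule covers all control data collection, and follow-up is part of it. The dates show that training had started before control follow-up ended. A control patient who came back to the outpatient clinic between T2 and T3 could have met staff already trained in the attachment approach. That bears on T1-T3, a named comparison for both primary outcomes, and on help-seeking and medication use, which have no T2 measurement to fall back on. Spillover of this kind would usually make controls resemble treated patients and so shrink the T1-T3 difference.

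A second issue is independent of the first. One block follows the other, with no concurrent controls. Keeping training away from controls deals with spillover; it does not deal with changes in referral, staffing or co-treatment between 2012-13 and 2014-15. Such changes would enter the group difference, in either direction, to the extent that the named covariates do not capture them. The Potential limitations section discusses training intensity, the short programme and the setting, but not change over time.

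**Working it through.** **1. The dates side by side** (all from Trial status)

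| Event | Period |
|---|---|
| Control T1 and T2 | March 2012 to October 2013 |
| Staff training | November 2013 to May 2015 |
| Intervention T1 and T2 | March 2014 to December 2015 |
| Control T3 questionnaires all sent | by May 2014 |

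Training starts after the last control T2, so no control treatment, T1 or T2 falls inside the training period. Control T3 dispatch overlaps training for about 6 to 7 months (November 2013 to May 2014), and longer if return dates are counted. Intervention recruitment also starts before control T3 is finished.

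**2. How many controls are affected.** The plan gives no figure, so this rests on assumptions: even recruitment, a first T2 about one month after March 2012 (the programme lasts four weeks), and T3 due six months after T2. Count months from 1 March 2012 = 0, so T2 runs from month 1 to month b. With training starting at month s, T3 falls after training began if T2 is later than s − 6:

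share = [b − (s − 6)] / (b − 1)

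| Last T2 (b) | Training start (s) | Share | Of 184 |
|---|---|---|---|
| 20 (end of October 2013) | 20 (start of November) | 6/19 = 31.6% | 58 |
| 20 | 21 (end of November) | 5/19 = 26.3% | 48 |
| 19 (end of September 2013) | 20 | 5/18 = 27.8% | 51 |
| 19 | 21 | 4/18 = 22.2% | 41 |

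The range is 22-32%, or about 41-58 patients before dropout.

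**3. Group and period.** Every control is in the first period and every intervention patient in the second. A design matrix with an intercept, group and period has rank 2 rather than 3, so the data cannot separate the two effects.

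**4. What a period shift would do.** Suppose the true intervention effect is zero and the outcome shifts by δ SD between blocks (δ is assumed). For an unadjusted two-sided t-test at 0.05, the noncentrality is δ / √(1/n₁ + 1/n₂). At δ = 0.2 and 93 per group it is 0.2 / √(2/93) = 1.364; at 184 and 194 it is 0.2 / √(1/184 + 1/194) = 1.944.

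| Assumed shift | 93 per group (planned minimum) | 184 and 194 (T1 counts) |
|---|---|---|
| 0.1 SD | 10% | 16% |
| 0.2 SD | 27% | 49% |

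The nominal rate is 5%. For scale, the planned effect in the Sample size calculation section is 0.4.

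**5. Checking the possible remedies** (even monthly admissions assumed: March 2012 to September 2013, and March 2014 to November 2015)

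- *Leaving out the late controls.* Mean admission is month 9 for controls and month 34 for the intervention block, a gap of 25 months. Dropping the last 6 of 19 control months moves the control mean to month 6 and the gap to 28. Losing 41-58 controls leaves 143-126, and the standard error of the group difference rises by a factor of 1.07-1.11, since √(1/143 + 1/194) / √(1/184 + 1/194) = 1.07 and the same ratio with 126 is 1.11.
- *Adding admission date to the group comparison.* The Potential limitations section expects therapists to improve during the study and effects perhaps to appear only late in the intervention block. If the true effect rises linearly from 0 to 0.8 SD over that block (mean 0.4, assumed) and there is no secular trend, a common linear date term absorbs the rise. The date-adjusted group coefficient is then about −0.16, the wrong sign.

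**The case against.** The strongest reply is that the isolation claim concerns spillover and that, where it matters most, it is true: control treatment and T2 ended before any training, and the pain hypothesis at the end of the Background section is stated for change from before to after treatment. This stands. A reader might infer from the overlap that isolation fails altogether; the dates do not support that, because only T1-T3 is affected.

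A reader might also infer that controls were in fact contaminated. The article does not say so. The programme lasts four weeks, T3 questionnaires were sent out, and no return visits are described. Contact is possible, not shown.

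The sequential, non-randomised design is openly declared with reasons, and both blocks have been recruited, so criticising the design as such achieves little. The analysis uses change from T1 and adjusts for demographic and clinical covariates given as examples, so measured case mix is partly handled. Both points stand. What remains is unmeasured change over time, which no covariate can separate from group and which the limitations omit.

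Calendar confounding might be read as disproving the no-spillover claim. It does not; the two are different problems. Nor does the Background hypothesis about insecurely attached patients overclaim causality: its wording on attribution says which patients are expected to drive the difference, not that other causes are excluded.

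Finally, *data collection* may have been meant as T1 and T2 only. If so, the wording correction settles the contradiction, but T1-T3 still lacks the protection that the Design section states without qualification.

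**Conclusion.** The concern holds in a limited form. The timing statements in the Abstract and the Design section contradict the dates in Trial status as far as T3 is concerned, and this needs no assumption. Protection from spillover holds for T1-T2. For T1-T3, including help-seeking and medication use, it cannot be claimed for about 22-32% of controls (41-58 of 184 before dropout, assuming even recruitment and T3 six months after T2). The size of any spillover is unknown.

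As a separate matter, group is completely aliased with calendar period. The 10-27% false-positive range at 93 per group rests on an assumed shift of 0.1-0.2 SD and an unadjusted t-test; it shows sensitivity and is not an estimate of bias in this trial. The fault lies in the unqualified assurance and in the silence on secular change, not in the choice of a sequential design.

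**What to change.** 1. In the Abstract and the Design section, limit the timing statement to treatment, T1 and T2 of the control group. Qualify the assurance in the Design section so that it covers spillover up to T2 only. This is a wording change.
2. Add a T1-T3 sensitivity analysis that leaves out controls whose T3 fell due in or after November 2013. The cost is some precision (standard error up by about 7-11% before dropout) and a wider mean calendar gap between blocks, from about 25 to up to 28 months. It should therefore sit beside the full T1-T3 comparison and not replace it.
3. Within the control block only, regress baseline-adjusted change on admission date and report the slope with its confidence interval as a check on secular drift. Do not add a common date term to the group comparison, because the plan expects the effect to grow during the intervention block and such a term can reverse its sign.
4. List secular change among the limitations and word the conclusions as a before-after difference between cohorts.

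Items 2 and 3 need only admission and follow-up dates, which the clinic should already hold. Nothing in the conduct of the study changes.
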